## Abstract

**Background:**

Nutrition during early childhood is critical for growth, development, and long-term well-being, with age-appropriate complementary feeding playing a pivotal role in meeting a child’s nutritional needs. Despite concerted efforts through national programs in India, gaps persist in complementary feeding practices, contributing to the enduring burden of undernutrition. This study aims to address these gaps by developing an intervention package comprising state- and district-specific improved take-home rations (THRs) provided under the Integrated Child Development Services (ICDS) alongside socio-culturally tailored social and behaviour change communication (SBCC) strategies to improve nutrition among children aged 6–36 months.

**Methods:**

The study will be conducted in one selected district from each of six Indian states—Karnataka, Madhya Pradesh, Maharashtra, Meghalaya, Odisha, and Rajasthan. The study comprises three sequential phases. In the first phase, formative research will explore current dietary practices of children aged 6–36 months, including THR uptake, as well as perceptions and challenges related to existing THR provision under ICDS and SBCC initiatives from both supply- and demand-side stakeholders. In the second phase, insights from formative research will inform co-development of an intervention package comprising optimized THR formulations and a multi-level SBCC strategy through an iterative and participatory process, which will be piloted to assess feasibility and acceptability. In the final phase, a two-arm cluster randomized controlled trial (cRCT) will evaluate the effectiveness of the intervention in improving nutritional status and complementary feeding practices compared to existing THR and SBCC strategies. cRCT will comprise: (1) a longitudinal cohort of children aged 6–18 months receiving the intervention for 18 months, with follow-up at baseline, 6, 12, 18, and 24 months to assess outcomes at individual level; and (2) repeated cross-sectional surveys of all children aged 6–36 months residing in study clusters at baseline and 6-month intervals up to 24 months to capture population-level changes.

**Discussion:**

The study will demonstrate the effectiveness of improved THR products combined with socio-culturally relevant SBCC strategies in improving feeding practices and nutritional status of children aged 6–36 months, while also assessing cost-effectiveness. By prioritizing local acceptability, sustainability, and use of locally available nutrient-rich foods aligned with regional dietary preferences, the intervention aims to bridge the gap between policy intentions and community practices. Findings will inform future THR reform and complementary feeding initiatives in India.

**Clinical trial registration:**

https://ctri.nic.in/Clinicaltrials/searchbyctri.php, identifier CTRI/2024/10/075472.

## Background

1

Nutrition is central to achieving the Sustainable Development Goals (SDGs), with at least 12 of the 17 SDGs incorporating nutrition-related indicators (1). Despite economic growth and numerous policy initiatives, India continues to bear nearly one-third of the global burden of undernutrition (2). Most recent prevalence estimates for stunting (35.5%), wasting (19.3%), and underweight (32.1%) in children under five in India remain high, exceeding World Health Organization (WHO) thresholds for public health concern (>30% for stunting, >15% for wasting) (3).

The first 1,000 days of life represent a critical window for physical and cognitive development, laying the foundation for lifelong health (4). Although the benefits of timely and appropriate complementary feeding during this period are well documented, significant gaps remain between recommended and actual practices, particularly in low- and middle-income countries (LMICs) (5–11). In India, the Integrated Child Development Services (ICDS) scheme through its Supplementary Nutrition Programme (SNP) provides take-home rations (THRs) for children aged 6–36 months and pregnant and lactating women, along with hot cooked meals for preschool children aged 3–6 years, to improve nutritional status (12). However, program impact is often constrained by persistent challenges such as suboptimal food quality, poor complementary feeding practices, inappropriate timing, and inadequate portion sizes (10, 13–16). To address these gaps, there is growing recognition of strengthening social and behaviour change communication (SBCC) components as a critical and complementary strategy in nutrition programs. Evidence shows that integrating SBCC into nutrition programs can enhance caregiver knowledge, promote appropriate feeding behaviours, and improve dietary and nutritional outcomes (17–23).

Recognizing the gaps, NITI Aayog, the Government of India’s apex public policy think tank has advocated for strengthening the delivery of nutritious THRs, improving production, supply chain mechanisms, and SBCC to enhance the effectiveness of ICDS (24). Recent initiatives, such as Saksham Anganwadi and Mission Poshan 2.0, aim to align supplementary nutrition with updated requirements (25). Nevertheless, persistent issues remain, including poor nutrient composition of THRs, intra-household sharing of rations, and limited cultural acceptability (9, 10, 26). The Government of India, in January 2023, revised Schedule II of the National Food Security Act (2013), introducing updated nutrition norms that go beyond energy and protein, incorporating quality of protein, healthy fats, carbohydrates, and seven essential micronutrients (27).

Addressing undernutrition requires interventions that move beyond improving food composition to also consider socio-cultural and behavioural factors influencing feeding practices. Household dynamics, caregiving practices, and community beliefs significantly shape dietary behaviours. Therefore, context-specific, culturally appropriate SBCC strategies that can enable and engage communities are essential to foster uptake and ensure sustained improvements in child nutrition (28–31).

The present study aims to improve the nutritional status of children aged 6–36 months through an integrated approach that enhances the nutritional quality of THRs and promotes complementary feeding practices using tailored SBCC strategies. The study proposes to develop and evaluate the effectiveness of the improved, state- and district-specific THRs in combination with socio-culturally appropriate SBCC strategies to enhance the nutritional status of children aged 6–36 months across selected sites in six Indian states.

Study objectives are defined as:

Primary objective:

1. To evaluate the effectiveness of an integrated intervention package, comprising improved THR and SBCC strategy, targeted at children aged 6–36 months (and their caregiver/households) on weight-for-age z score (WAZ) after 18 months of implementation, compared to the existing THR and SBCC strategy.

Secondary objectives:

2. To evaluate the effect of the intervention package targeted at children aged 6–36 months (and their caretakers/households) compared to the existing THR and SBCC strategy after 18 months of implementation on length/height-for-age z score (LAZ/HAZ), weight-for-height/length z score (WHZ/WLZ), the prevalence of underweight (WAZ < -2SD), wasting (WHZ/WLZ < -2 SD), stunting (LAZ/HAZ < -2 SD), infant and young child feeding practices (IYCF) (such as minimum meal frequency, minimum dietary diversity, and minimum acceptable diet), child morbidity indicators, and caregiver knowledge, skills, practices, and behaviour towards infant and young child feeding practices.3. To document the incremental cost-effectiveness of the integrated intervention package compared to the existing THR and SBCC strategy in the study districts.

## Methods and materials

2

This multicenter study will be conducted in three sequential phases over a period of 48 months. The first phase will involve formative research to explore and understand the perceptions, practices, and attitudes of different stakeholders, as well as the challenges related to the existing THR and SBCC efforts for addressing the nutritional status of children aged 6–36 months, using an exploratory cross-sectional design with embedded mixed methods. In the second phase, an improved and context-specific THR and SBCC intervention package will be developed and piloted using a participatory research approach with mixed methods. The final phase will involve a two-arm cluster randomized controlled trial (cRCT) to evaluate the effectiveness of the developed intervention package.

### Study setting

2.1

All phases of the study will be conducted in one selected district from each of six Indian states, ensuring representation across diverse geographic regions, cultures, and dietary diversity. Study activities at each site will be implemented by a consortium of institutions. Study sites, including selected states and districts, are illustrated in Table 1 and Figure 1.

**Table 1 tab1:** The study districts selected for the study.

Region	State	District	Implementing institution
East	Odisha	Nuapada	All India Institute of Medical Sciences, Bhubaneshwar, Odisha, India and The INCLEN Trust International, New Delhi, India
West	Maharashtra	Wardha	JN Medical College, Datta Meghe Institute of Higher Education and Research, Wardha, Maharashtra, India
North	Rajasthan	Jodhpur	ICMR—National Institute of Nutrition, Hyderabad, Telangana, India
South	Karnataka	Shivamoga	St John’s Research Institute, Bengaluru, Karnataka, India
Central	Madhya Pradesh	Hoshangabad	All India Institute of Medical Sciences, Bhopal, Madhya Pradesh, India
Northeast	Meghalaya	Ri Bhoi	The George Institute for Global Health, New Delhi, India

**Figure 1 fig1:**
[figure not shown]
Study sites—selected states and the districts.

### Phase I: formative research

2.2

Exploratory research will be undertaken over a period of six to seven months to assess the current status of complementary feeding practices and THR implementation and uptake, and to generate context-specific, evidence-based insights. The research will be driven by four key objectives:(1) to assess the current provisions, quality, implementation, and uptake of THR under ICDS program in selected states; (2) to explore the perceptions of key stakeholder including policymakers, program implementers, frontline workers, vendors, and civil society members regarding the challenges and gaps in the THR products and program implementation; (3) to assess IYCF feeding and dietary practices, including locally prevalent, traditional, and culturally embedded complementary feeding practices, and positive feeding behaviours among children aged 6 to 36 months, and to document perspectives of caregivers and key community stakeholders; and (4) to evaluate the nutritional and chemical profile of the existing THR products. These objectives will be achieved through various activities outlined in Table 2.

**Table 2 tab2:** Components of formative research.

Activity	Tools/methods	Key outputs
Review of existing literature	Desk review	THR policies, guidelines, composition, supply chain, SBCC strategies, best global practices, and relevant SBCC theories/models
Mapping of the THR supply chain and key stakeholders engaged in the selected district	Net mapping tool (32); Key informant interviews (KIIs) with the stakeholders identified through stakeholder mapping and snowball sampling.	Current THR provision (ingredients, nutrition profile), end-to-end supply chain from procurement to distribution, logistics and costs, etc.
Observations related to program implementation	Observation checklists; In-depth interviews (IDIs) and KIIs.	Existing training standards, adequacy of personnel, infrastructure, and SBCC strategies.
Qualitative inquiries with supply-side stakeholders	IDIs, focused group discussion (FGDs) (until data saturation).	Perceptions of supply-side actors (program implementers, frontline workers like anganwadi workers (AWWs), anganwadi helpers (AWHs), vendors, civil society members, SHG, etc.) on challenges and gaps in current THR composition and SBCC delivery.
Qualitative inquiries with demand-side stakeholders	IDIs, FGDs, and food free-listing guides.	Caregiver and community perceptions regarding the dietary practices, complementary feeding, children’s food preferences, local and indigenous foods, exploration of locally prevalent positive traditional feeding practices practiced by positive deviant households, acceptability and uptake of current THR and SBCC activities, and their expectations for improvement.
Household survey along with KABP	KABP questionnaire (estimated sample size, *N* = 220 children aged 6–36 months); 24-h dietary recall tool (2 nonconsecutive days).	Individual level—caregivers’ KABP regarding complementary feeding, diet diversity, frequency and quantity of feeding, THR use, nutrition intake of children. Household level—socio-demographic and environmental factors likely to affect complementary feeding and nutritional status of the children.
Market survey	Market survey tool (33)	Price of locally available foods at the community level.
Laboratory analysis of existing THR	Batch-wise macronutrient and micronutrient analysis; FSSAI-certified labs; samples to be sent to a second FSSAI-certified laboratory for quality assurance.	The nutritional, chemical, and microbiological profile following Schedule II of the National Food Security Act, 2013, revised in January 2023 (27).

IDI, In-Depth Interview; KII, Key Informant Interview; FGD, Focused Group Discussion; KABP, Knowledge, Attitudes, Beliefs, and Practices; FSSAI, Food Safety and Standards Authority of India; AWW, Anganwadi Worker; AWH, Anganwadi Helper. Net-Map is a group interview-based tool that helps in understanding the interplay of complex formal and informal networks, stakeholder influence, and power dynamics through visualization exercises. In this study, an adapted Net-Map tool will be used to map the Take-Home Ration (THR) supply chain under the ICDS Supplementary Nutrition Program, identify key actors at policy and implementation levels, and understand their roles, interconnections, and influence across the supply chain.

During this phase, the study will document traditional complementary foods, recipes, preparation methods, feeding norms, and caregiving and feeding practices, and identify positive behaviours through in-depth discussions with caregivers, particularly mothers of well-nourished children from the local community. These insights will inform the contextually appropriate practices that can be highlighted and promoted as part of the social and behaviour change communication strategy of large-scale supplementary feeding programmes. The evidence generated during the formative phase will be instrumental in informing the development of optimized THR compositions and the design of the SBCC strategy tailored to specific state and district contexts, ensuring cultural appropriateness, local relevance, and cost-effectiveness.

### Phase II: development and piloting of the improved integrated intervention package

2.3

Phase 2 will span six months and will involve a sequence of activities to develop, refine, and test the intervention package. The flow of activities in phase 2 is illustrated in Figure 2.

**Figure 2 fig2:**
[figure not shown]
Flow of activities in phase 2.

#### THR recipe optimization and sensory evaluations

2.3.1

This step will involve finalizing the THR formulations (2–3 variants) based on nutritional modelling and stakeholder consultations. A systematic process will be undertaken to select ingredients and formulate THR blends that meet energy and nutrient standards (see Supplementary Table 1). Field-level testing will be carried out through cooking demonstrations to assess the palatability, texture, and ease of preparation of the proposed enhanced THR recipes, along with sensory evaluations with caregivers using Likert-type or hedonic scales. Standardized, structured sensory evaluation questionnaires will be administered by trained field investigators immediately following the cooking demonstrations and tasting sessions. These questionnaires will capture caregiver ratings of appearance, aroma, texture, taste, ease of preparation, and overall acceptability for each recipe. Data will be collected at the individual caregiver level using paper-based or electronic forms and entered into a centralized database for analysis. Caregiver feedback on ingredient availability, cooking feasibility, and feeding challenges will be documented. Simultaneously, assessments of existing household practices, including current dietary practices, food access, and cultural beliefs influencing feeding, will also be conducted using structured interviews and food preference ranking exercises. In addition, the nutritional status of the selected children will be assessed.

These activities will yield a refined list of nutritionally enhanced, culturally acceptable THR products and recipes tailored to local food habits and seasonal availability, along with household-specific dietary contexts established for subsequent Trials of Improved Practices (TIPs) engagement.

#### Co-development of evidence-based, contextual, multi-level SBCC strategy

2.3.2

The social and behaviour change communication strategy, as part of the intervention package, will be developed utilizing the Socio-Ecological Model (34–36). In addition, behavioural theories such as Social Cognitive Theory and Nudge Theory will guide the design of SBCC activities, ensuring that the strategy is both locally acceptable and context-specific by addressing barriers identified during the formative phase (37, 38). Since behaviours are shaped by complex influences at multiple levels—individual, interpersonal, organizational, community, and policy- it is critical that the SBCC strategy addresses determinants across these domains. Previous studies have identified potential reasons for the limited consumption of take-home rations across these levels (10, 13, 15, 26, 39, 40). They have also explored various approaches to promote IYCF practices and improve the uptake of supplementary feeding (21, 24, 30, 31, 41–43). Building on this evidence, the improved strategy will give primary emphasis to behaviour change at the individual and interpersonal levels, focusing especially on caregivers while also engaging relevant stakeholders across higher levels of influence. The SBCC framework to promote IYCF practices and utilization of THR is illustrated in Figure 3.

**Figure 3 fig3:**
[figure not shown]
SBCC framework to promote IYCF practices and utilization of take-home rations. Factors shown on the left depict potential reasons for the low consumption of take-home rations (THR) identified in the literature (9, 10, 13, 15, 26, 39, 40) while those on the right represent approaches and strategies reported in studies to promote IYCF practices and enhance supplementary feeding utilization (21, 24, 30, 31, 41–43). This SBCC framework is adapted with permission from UNICEF’s Socio-Ecological Model (34–36).

The enhanced SBCC components will aim to strengthen maternal knowledge and feeding behaviours, thereby improving IYCF practices and use of improved THRs. In addition, they will aim to elevate the capacity and engagement of frontline workers and other key stakeholders.

#### Trials of improved practices (TIPs) approach for iterative refinement

2.3.3

Five 1-week cycles of TIPs will be conducted with households over the seven weeks to study the feasibility, adherence, acceptability, and willingness to adopt the proposed recipes and SBCC messages (44). Each cycle will provide insights to iteratively adapt the intervention, guided by caregiver feedback and local constraints. Field staff will engage with selected households (approximately 60 households) in trying out the optimized THR recipes and SBCC messages in real-life settings. Structured weekly follow-up visits will be conducted with these households to document adherence, identify barriers, and capture user-driven modifications. Recipe acceptability, feeding quantity, preparation effort, and caregiver perceptions will be evaluated using observation checklists, meal logs, and structured feedback cards. Real-time feedback will be used to adapt recipes and refine SBCC messages around responsive feeding, dietary diversity, and hygiene.

The expected outputs from these activities include detailed documentation of recipe adherence and barriers across different nutritional status strata. Outputs will also encompass refinement of SBCC messages tailored to local beliefs, knowledge gaps, and motivational levers, as well as inputs for adjusting portion sizes and feeding frequency in relation to child nutritional status. All field investigators administering the questionnaires will undergo standardized training to ensure uniform application of tools and minimize interviewer bias.

#### Synthesis of findings and stakeholder consultation

2.3.4

This 4-week period will focus on triangulating findings from the field and refining the integrated package through participatory stakeholder discussions. Findings from the TIPs cycles, including caregiver feedback, recipe adherence scores, and SBCC trial outcomes, will be consolidated and shared with local stakeholders and program functionaries. Stakeholder consultations will then be conducted with ICDS and health functionaries and community leaders to validate the feasibility and acceptability of the proposed recipes and messages, and to identify operational bottlenecks and solutions for informing the intervention. This process will help co-develop and finalize the integrated intervention package, ensuring alignment with ground realities and programmatic logistics. It will also help provide a stakeholder-endorsed implementation plan covering supply-side considerations (e.g., ingredient sourcing, shelf life, and logistics, etc.).

#### Pilot testing of the integrated package

2.3.5

In the final step, the integrated package will be piloted for one complete monthly cycle to assess its operational viability and real-life consumption. The pilot will focus on monitoring supply chain functionality, actual consumption by target children, and implementation fidelity. THR packages will be distributed to the same ~60 households already engaged in Step 3.

A purposive sample of minimum 30 children aged 6–12 months and 30 children aged 13–36 months will be recruited from selected Anganwadi centres (AWCs), ensuring adequate representation from both rural and urban areas. Within the identified centres, efforts will be made to include all available cases of children with severe acute malnutrition (SAM) and moderate acute malnutrition (MAM). Efforts will also be made to ensure appropriate representation of Scheduled Caste/Scheduled Tribe (SC/ST) and non-SC/ST households during AWC and household selection.

Between 4–6 THR products will be evaluated during the pilot. Of these, 2–3 will be designed for normally nourished children and 2 for those with SAM or MAM. For each product, 2–3 recipe variations will be tested. Recipes will be served in age-appropriate portion sizes to younger children (6–12 months) and older children (13–36 months). Each product-recipe combination will be tested at least twice with adequate intervals, and the most consistent observations will be considered for analysis.

Over this one month, recipe preparation, feeding frequency, and child consumption will be monitored using daily food logs and periodic home visits. Acceptability, wastage, adherence, and practical challenges will be assessed, alongside feedback on implementation logistics from ICDS staff and caregivers.

Key indicators to be assessed include the quantity consumed per child per day across nutritional status strata (normal and MAM/SAM), barriers to preparation or uptake, and feedback on message retention and behaviour change initiation. The expected outputs from this phase include practical feasibility data for each recipe and SBCC component under program conditions, insights into the actual quantity of THR consumed by children across different malnutrition categories, and evidence to guide adjustments in ration size (currently set as double ration for malnourished children) to inform ICDS feeding guidelines. Ultimately, 2 to 3 THR products will be finalized to be used in the next study phase.

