#### Statistical analysis plan

2.3.6

Caregiver sensory evaluation scores obtained through Likert-type or hedonic scales will be treated as ordinal data. Summary statistics will be presented as medians and interquartile ranges. Differences in sensory preference scores across THR recipes will be assessed using non-parametric tests, including the Kruskal-Wallis test, as appropriate. Changes in acceptability and adherence scores across repeated TIPs cycles will be analyzed using the Friedman test.

Qualitative analysis will be performed by thematic coding of barriers and caregiver feedback. Content analysis of qualitative responses on cultural appropriateness and ingredient feasibility will be done.

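### The pilot keeps only the repeat tests that agree best, by an undefined rule, which understates within-child variation and can bias mean intake in an unknown direction

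*Protocol article*

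**What the plan says.** Section 2.3.5 of the protocol article describes a one-month pilot in about 60 households, meant to show how much children actually eat, what is wasted and how acceptable the products are. The design is: "A purposive sample of minimum 30 children aged 6–12 months and 30 children aged 13–36 months will be recruited"; "Between 4–6 THR products will be evaluated during the pilot"; "For each product, 2–3 recipe variations will be tested". The rule at issue follows: "Each product-recipe combination will be tested at least twice with adequate intervals, and the most consistent observations will be considered for analysis". The section does not say what counts as consistent, who decides, or whether the choice is made within a child, within a combination or across children.

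The section makes the quantity eaten per child per day, by nutritional status, a key indicator. It lists among its outputs "evidence to guide adjustments in ration size (currently set as double ration for malnourished children) to inform ICDS feeding guidelines", and it ends: "Ultimately, 2 to 3 THR products will be finalized to be used in the next study phase". Daily food logs and periodic home visits are also planned. The section does not say whether the consistency rule applies to them.

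On the sensory ratings, section 2.3.1 says: "These questionnaires will capture caregiver ratings of appearance, aroma, texture, taste, ease of preparation, and overall acceptability for each recipe". Section 2.3.6 says: "Differences in sensory preference scores across THR recipes will be assessed using non-parametric tests, including the Kruskal-Wallis test, as appropriate", and then names the Friedman test for scores repeated over TIPs cycles. It names no test for the pilot consumption data.

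**The concern.** The rule is stated affirmatively, so it is not a detail left to a fuller document. It decides which results count by looking at the results. A child who eats a recipe one day and refuses it the next is exactly the evidence a consumption and acceptability pilot should collect, and that pattern is the one most likely to be discarded. What remains looks steadier than the truth. Because the criterion is undefined, two analysts could retain different data.

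At stake are the product-recipe results behind the choice of two to three products for the cluster trial, and possibly the ration-size evidence. With a minimum of 30 children in each age group, discarding tests also costs precision.

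A smaller question concerns the sensory scores. If one caregiver rates several recipes, the ratings are paired, and Kruskal-Wallis treats them as independent groups.

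**Working it through.** The document gives no sample-size, power or error figure for this phase, so there is none to reproduce. It does give the minimum number of tests (two), 4–6 products and 2–3 recipes each. That makes 4 × 2 = 8 to 6 × 3 = 18 product-recipe combinations, and at least 16 to 36 tests over them. Refusal rates, intake distributions, correlations and effect sizes below are assumptions.

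**1. Two tests (the stated minimum).** The difference between results A and B is the same whichever is taken as reference, so agreement cannot favour one. If the rule is applied by dropping discordant pairs, and each test is refused independently with probability p:

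- share of pairs dropped = 2p(1 − p)
- refusal rate among retained tests = p² / [p² + (1 − p)²]

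| True p | Pairs dropped | Apparent refusal |
|---|---|---|
| 0.10 | 0.18 | 0.01/0.82 = 0.012 |
| 0.20 | 0.32 | 0.04/0.68 = 0.059 |
| 0.30 | 0.42 | 0.09/0.58 = 0.155 |

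Independence is the unfavourable case. If refusals cluster in the same children, fewer pairs disagree and the distortion shrinks.

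**2. Three tests, majority result kept.** Apparent refusal = 3p² − 2p³ = 0.028, 0.104 and 0.216 for p = 0.10, 0.20 and 0.30.

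**3. Three tests, closest two kept** (simulation, 400,000 triplets of standard normal replicates):

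- Apparent within-child SD is 0.42 against a true value of 1.
- The SD of the retained mean is 0.80, against 0.58 for the mean of all three. The variance ratio from the unrounded values is (0.798/0.578)² ≈ 1.9.
- The mean is unbiased, because the distribution is symmetric.

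**4. Direction of bias in mean intake (closest two of three).**

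| Assumed intake when eaten | Refusal rate | Retained mean against true mean |
|---|---|---|
| Normal, 60 g, SD 12 g | 10–30% | 8–11% too high |
| Same | 60% | 13% too low |
| Lognormal, sigma 0.3 | 10–30% | 3–6% too high |
| Lognormal, sigma 0.6 | 10–30% | 12–16% too low |
| Lognormal, sigma 0.6 | none | 1.04 against 1.20, about 13% too low |

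The sign changes with inputs the document does not supply.

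**5. Kruskal-Wallis against Friedman, if every caregiver rates every recipe** (1,500 runs per setting, 60 caregivers, 9-point scale, one recipe shifted by 0.4 SD, two-sided 0.05). The number of caregivers giving sensory ratings is not stated; 60 is borrowed from the TIPs and pilot households.

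| Recipes | Within-caregiver correlation | Kruskal-Wallis type I error | Kruskal-Wallis power | Friedman power |
|---|---|---|---|---|
| 3 | 0 | 0.043 | 0.57 | 0.48 |
| 3 | 0.3 | 0.014 | 0.57 | 0.67 |
| 3 | 0.5 | 0.004 | 0.54 | 0.80 |
| 3 | 0.7 | 0.000 | 0.52 | 0.96 |
| 6 | 0.3 | 0.009 | 0.43 | 0.64 |
| 6 | 0.7 | 0.000 | 0.26 | 0.97 |

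Friedman's type I error stays between 0.04 and 0.06. With positive correlation Kruskal-Wallis is conservative; with none it is slightly the more powerful test.

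**The case against.** This is a purposive feasibility pilot, and no passage makes a p-value the rule for choosing products. Nutritional modelling, stakeholder consultation, caregiver feedback, cost and regulatory approval all play a part. Daily food logs run alongside the repeat tests. That limits the consequences, but it does not justify selecting repeats on their agreement.

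Four stronger readings are tempting, and the document does not support them:

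- **Consumption will be reported as too high.** The sign depends on the unstated intake distribution and refusal rate. Consistent refusals would also be kept.
- **The 0.42 and 1.9 ratios describe this pilot.** They need at least three tests; only two are guaranteed.
- **The ration-size evidence is distorted.** The rule stands in the sentence on repeated product-recipe tests. Nothing says it filters the daily logs, which could supply the per-day quantity, so the link is possible and not established.
- **Kruskal-Wallis is plainly the wrong test and also harms the ration evidence.** Section 2.3.1 implies, but does not state, that one caregiver rates several recipes. Section 2.3.6 leaves room for other non-parametric tests where appropriate. The test concerns sensory scores, not intake, and the planned medians and interquartile ranges are unaffected.

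What stands is that the consistency rule is explicit, undefined and tied to the outcome, and that a better rule costs nothing in data collection.

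**Conclusion.** The point holds for the consistency rule. Followed as written, it understates within-child variation and inconsistent acceptance and loses precision. It can also bias mean intake in either direction. The sizes above are illustrations on assumed inputs and are not estimates for this pilot; the refusal figures also assume independent tests. The affected results feed the choice of products and may feed the ration-size evidence.

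The Kruskal-Wallis point is secondary and conditional on the same caregivers rating several recipes. The error would then be to miss real preferences, with no excess of false ones.

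Both matters belong to Phase II and leave the validity of the Phase III primary analysis untouched.

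**What to change.** In section 2.3.5, delete the clause restricting analysis to the most consistent results. State instead that every test of every product-recipe combination is analysed, refusals included, either as the mean of all tests per child or in a mixed model with child as a random effect. Report within-child variation alongside mean intake.

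In section 2.3.6, state whether each caregiver rates several recipes. If so, use the Friedman test for recipe comparisons, or an ordinal mixed model with caregiver as a random effect if not every caregiver rates every recipe.

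The cost is wording only, with no extra visits or data. The price is that reported consumption will look more variable.
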